**Fig 1. SPIRIT Flowchart**

|  | **STUDY PERIOD** | | | | | | | |
| --- | --- | --- | --- | --- | --- | --- | --- | --- |
|  | **Enrolment** | **Allocation** | **Post-allocation** | | | | | **Close-out** |
| **TIMEPOINT*** | ***-t_2_*** | ***-t_1_*** | ***t_0_*** | ***t_1_*** | ***t_2_*** | ***t_3_*** | ***t_4_*** | ***t_5_*** |
| **ENROLMENT:** |  |  |  |  |  |  |  |  |
| **Eligibility screen** | X |  |  |  |  |  |  |  |
| **Informed consent** | X |  |  |  |  |  |  |  |
| **Baseline assessment** | X | X |  |  |  |  |  |  |
| **Allocation** |  | X |  |  |  |  |  |  |
| **INTERVENTIONS:** |  |  |  |  |  |  |  |  |
| ***[Brief mindfulness training]*** |  |  |  |  |  |  |  |  |
| ***[Relaxation training]*** |  |  |  |  |  |  |  |  |
| **ASSESSMENTS:** |  |  |  |  |  |  |  |  |
| ***[Demographic data]*** | X |  |  |  |  |  |  |  |
| ***[Primary outcome variables]*** | X | X | X | X | X | X | X | X |
| ***[Secondary outcome variables]*** | X | X | X | X | X | X | X | X |
| ***[Daily records during intervention]*** |  |  | X | X | X | X | X | X |

**Fig 2. SPIRIT schedule of enrolment, interventions and assessment.**

** Note: -t2, -t1, baseline (complete measurements twice to get average); t0, post-intervention; t1- t5, 1-week, 1-month, 4-month, 6-month,1-year follow-up.*

1. ***Research background. [usually adopting a four-part structure: (1) Overview of the health problem or research question: definition of the health problem, epidemiological data, etiology, natural history of the disease, disease burden, etc.; (2) Scientific hypothesis: mechanism or principle; (3) Clinical application, for example, treatment studies should explain the treatment methods; (4) Necessity of the study based on current evidence, explaining why this study needs to be conducted]***

According to the latest data from the China Internet Network Information Center [[1](#_ENREF_1" \o "Center, 2022 #684)], by June 2022, the scale of online game users in our country still exceeded half of the total internet user base, reaching 552 million, among whom mobile games dominated, accounting for 60.9% of underage gamers [[2](#_ENREF_2" \o "Center, 2021 #685)]. Unlike substance addiction, which is induced by addictive substances, internet gaming disorder (IGD) is considered a behavioral addiction, characterized prominently by uncontrollable gaming behavior leading to emotional distress, neglect of academic or life responsibilities, and damage to interpersonal relationships, causing serious negative impacts on both individuals and society [[3](#_ENREF_3" \o "Ko, 2020 #686)]. According to the dual-process model, cognitive-behavioral model, and I-PACE model in addiction theory, it is concluded that emotional and cognitive mechanisms jointly contribute to the development and maintenance of gaming addiction, with cue-induced craving and diminished executive function closely related to IGD. Executive function regulation is also required for cue-induced craving, making executive function a critical area of research in IGD. The primary behavioral diagnostic feature of IGD is excessive gaming behavior despite the negative consequences, and behind this behavioral dysfunction lies functional impairment. Studies using fMRI on individuals with IGD have found abnormalities in brain structures such as the dorsolateral prefrontal cortex, anterior cingulate cortex, and orbitofrontal cortex, areas closely associated with executive function. However, studies on the executive function of IGD individuals have mainly focused on the subcomponent of inhibitory control, with less attention given to switching and updating components, particularly regarding the cognitive flexibility represented by switching, which remains controversial in the field of internet gaming addiction. To better explore the neurobiological mechanisms related to internet gaming addiction, it is necessary to investigate all three subcomponents of executive function.

Mindfulness, as an effective addiction treatment approach, has been widely applied in interventions for addiction and relapse, improving craving and maladaptive cognition in individuals with IGD [[4](#_ENREF_4" \o "Li, 2017 #687)], and has been proven to significantly enhance prefrontal cortex function, which is closely related to executive function. Individuals can improve overall executive function by initiating attention monitoring processes, strengthening working memory, and increasing cognitive flexibility in task switching, thus reducing impulsivity and addictive behaviors. Research on mindfulness interventions concerning executive function has primarily targeted populations such as patients with brain injuries, children with underdeveloped brain mechanisms, and elderly individuals with declining brain functions; there is less research on normally developed, healthy adults, especially within the addicted population, where the focus has largely been on smokers rather than individuals with IGD. Moreover, due to the time-consuming nature and face-to-face requirements of mindfulness interventions, the demand for short-term self-guided practices has increased. Existing research has confirmed that single-session and five-minute brief mindfulness interventions can improve health outcomes.

Currently, whether the three subcomponents of executive function in individuals with IGD are impaired, and whether mindfulness interventions can improve executive function and related brain mechanisms in IGD populations and normal healthy populations, lacks sufficient in-depth investigation. This study proposes to use a randomized controlled trial design to explore the effects of a one-week focused breathing meditation practice on executive function. On one hand, this may address the issue of low acceptance due to the long duration of mindfulness interventions, and on the other hand, exploring brain function mechanisms could provide more targeted intervention strategies for executive function research.

1. ***Objective***

Through the use of scales, behavioral data, and EEG data, this study aims to investigate whether the three sub-components of executive function in individuals with internet gaming addiction are impaired. Furthermore, it will conduct a one-week focused breathing meditation intervention to explore the effectiveness of concise mindfulness on executive function and its impact on brain function mechanisms. This endeavor will provide more targeted intervention strategies for research into executive function.

1. ***Inclusion and exclusion criteria. [Inclusion criteria define the main body of the study and determine the representativeness of the study population; exclusion criteria define individuals within the study population that may affect the study and determine the homogeneity of the study population]***

Inclusion criteria:

(1) Right-handedness;

(2) Normal vision or corrected-to-normal vision;

(3) Age between 18 and 40 years;

(4) Good mental and physical health (PHQ-9 total score < 20, GAD-7 total score < 11);

(5) Absence of other addictions (e.g., smoking, alcohol, gambling);

(6) For individuals with internet gaming disorder (IGD): Internet Addiction Test (IAT) score ≥ 50, DSM-5 score ≥ 5, gaming history exceeding 2 years, and gaming time of more than 14 hours per week;

(7) For recreational gamers: IAT score < 50, DSM-5 score < 5.

Exclusion criteria:

(1) Individuals with asthma, epilepsy, or a history of mental illness;

(2) Those who have taken steroid medications within the past three months;

(3) Individuals who have practiced meditation, yoga, Tai Chi, or Qi Gong for more than 20 hours in the past year or throughout their lifetime, attended meditation or yoga retreats, or participated in any meditation courses;

(4) Individuals unsuitable for electroencephalogram (EEG) testing due to metal implants, severe head injuries, contact dermatitis, or silicone allergies;

(5) Those with a PHQ-9 total score ≥ 20 or a GAD-7 total score ≥ 11;

(6) Individuals with other addictions (such as smoking, alcohol, or gambling);

(7) Individuals with strong adherence to a particular religious belief that would interfere with their ability to participate in the required meditation exercises;

(8) Individuals currently participating in similar trials or other neurophysiological studies.

1. ***Study design, design pattern diagram, with SPIRIT template attached. [Clearly state the design scheme used in this study, such as: consecutive case or single-arm design, cross-sectional study, case-control study, cohort study, including historical cohort study or prospective cohort study, nested case-control study, randomized controlled trial, clearly specify the type, such as parallel design, crossover design, factorial design, single-group design; for treatment studies, specify the type of research objective framework, such as superiority, equivalence, non-inferiority, exploratory]***

The current trial adopts a randomized controlled parallel design, with substantial literature supporting the moderate effect of brief mindfulness interventions on executive function [[5](#_ENREF_5" \o "Zhou, 2020 #694)]. Therefore, for the IGD population, this trial aims to demonstrate superiority under the condition of a brief mindfulness intervention compared to the control group. The trial comprises four stages: participant recruitment, baseline assessment, post-intervention measurement, and follow-up assessment, with corresponding evaluations conducted at the conclusion of each phase. A schematic diagram of the design is depicted in **Fig 3.** The trial has not yet commenced, and it is estimated that the entire process from initiating participant recruitment to completing data analysis and manuscript writing will take approximately one year.

**
[figure not shown]
**

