The estimation of Cohen's d is required, with the formula Cohen's d = (δ(Δ) / SDestimate). Referencing studies in similar populations [<https://www.ncbi.nlm.nih.gov/pmc/articles/PMC8939409/>], SDestimate is taken as 250. Therefore, the relevant command is pwr.t.test (d = cohen_d, sig.level = 0.05, power = 0.80, type = "paired", alternative = "two.sided"), resulting in a sample size estimate of 34. Thus, the estimated sample size for the experimental group should be no less than 34 individuals; considering a natural dropout rate of 20%, the sample size for the experimental group should be at least 41 individuals. A ratio of 2:1 will be used to include 20 recreational gamers in the intervention group. A total of 61 participants are required for the intervention group. In order to maintain appropriate comparability, we will recruit an additional 61 participants with matching demographic profiles and equivalent levels of IGD (Internet Gaming Disorder) severity for the control group. Thus, the study demands a cumulative participation of 122 individuals in total.

1. ***Methods of randomization and concealed allocation. [Randomization is used to reduce the risk of selection bias. Methods for generating random number sequences include computer software, random number tables, semi-random or pseudo-random methods (such as using dates, birthdays, or even/odd numbers of hospital visits). Please describe the individuals involved in generating random number sequences and the methods they use. Concealed allocation is used in treatment studies to reduce the risk of selection bias. Key steps in concealed allocation include having a designated person determine the allocation sequence, ensuring that this person is not involved in enrolling participants, and securely storing the allocation table. Please provide detailed descriptions of these steps. Central randomization is a robust method of concealed allocation. Describe the individuals and methods involved in determining the allocation sequence]***

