(1) In this study, the intervention period focused on breath meditation lasts for one week and serves as a concise mindfulness behavior training. The study will involve a baseline collection of EEG and other relevant data for all participants, a one-week training on the intervention content, collection of post-intervention EEG and other relevant data, and follow-ups (one week, one month, four months, six months, and one year after data collection post-intervention). During the follow-up phase, participants will undergo multiple mindfulness training sessions. Grouping will occur after the baseline data collection for participants is completed.

(2) The breath meditation training is the primary intervention method employed in this study. The design includes grouping into an experimental group and a control group: the experimental group (breath meditation training) and the control group (relaxation training). The recruited participants are from the same school, and their connections make it challenging to implement the criteria for double-blind randomization.

(3) The randomization process for this trial will utilize the random sequence generator available at random.org.

1. ***Blinding. [Blinding is used in treatment studies and diagnostic trials to reduce the risk of implementation bias and measurement bias. Implementing strict confidentiality measures, such as using placebos or simulating procedures, is an effective blinding method. If blinding is necessary and feasible for your study, describe the methods and procedures for implementing blinding]***

This trial involves group therapy, with participants being students from the same school. Therefore, it is possible that among participants who may know each other or even among those who do not, conversations related to the experimental training they are undergoing may arise. Additionally, maintaining blinding for the researchers is quite challenging, as they can easily be influenced by information related to the experiment during the process. As a result, it is not feasible to meet the double-blind requirements of clinical trials.

1. ***Outcome Measures. [Outcome measures are used to evaluate the results of a study and can include primary, secondary, and safety measures, including adverse events and reactions. Please describe the names of the measures, the methods of measurement, and the time points at which they are assessed]***

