Secondly, regarding adverse reactions during the EEG data collection process, if participants show physiological rejection responses or adverse emotions, researchers will immediately cease EEG data collection. Whether to continue the experiment will depend on ensuring the participants' health and safety, as well as their own willingness to either continue participating in the experiment or withdraw, with researchers recording the reasons. Subsequent follow-ups and interventions in this study will be communicated to participants after collective discussion among the research team before any decisions are made.

1. ***Ethical considerations. [This includes the selection of an ethics committee, approval procedures, informed consent process, registration time, and registration authority (please provide registration number after completion)]***

(1) Selection of the Ethics Committee: This trial has selected the ethics committee of the implementing institution, namely the Medical Ethics Committee of Kunming University of Science and Technology.

(2) Approval Process: Before the study begins, the research project proposal and related materials have been submitted for approval in accordance with the procedural requirements of the selected ethics review committee of the research institution.

(3) Informed Consent Process: Before the study begins, researchers will provide paper copies of the informed consent form to the participants and authorized agents, and address any questions related to the informed consent form to ensure that participants and authorized agents understand the content before signing the informed consent form.

(4) Registration Time: March 2024.

(5) Registration Institution: China Clinical Trial Registration Center.

1. ***Participant recruitment. [This includes the selection of recruitment locations, recruitment methods, the screening process, and the researchers conducting the screening]***
2. Recruitment Location: Chenggong Campus, Kunming Medical University.
3. Recruitment Method: This trial will use a combination of online and offline methods to recruit participants:

Offline: Conduct presentations in classrooms, create posters, and distribute flyers;

Online: Use campus platforms such as QQ Space, WeChat Moments, and the school's community bulletin board.

1. Screening Process: Participants will be selected based on their order of participation according to inclusion and exclusion criteria.

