8. Insert Active Electrodes: Correspondingly insert the labeled active electrodes into the designated electrode names marked on the EEG cap (make sure to carefully match the electrodes’ labels with the EEG cap). Wrap the CMS and DRL active electrode wires around the other electrodes' cables (3-5 wraps), and plug their connectors into the corresponding matching ports on the amplifier.
9. Confirm Connections and Start Data Collection: After confirming that the EEG software and hardware are properly connected, run the software to collect EEG data. Follow the software usage instructions and ensure the quality of the EEG data meets the required standards before starting the data collection. Save the EEG data to the computer or hard drive according to your naming format.
10. Intervention Content Training Process:

The researchers of this study will collaborate with professional psychological teachers to conduct a week-long intervention content training and multiple training sessions during the follow-up phase.Before each practice session begins, participants will be reminded of the time and location of the practice, and the researchers will conduct on-site check-ins. Training for the intervention content will be provided for one week by the teachers from the Student Mental Health Education and Counseling Center, along with multiple training sessions during the follow-up phase. Professional psychological teachers will guide the training, and the content practiced each day will be sent to the participants' group after each session for continued practice.

1. ***Statistical analysis methods. [Select appropriate statistical analysis methods based on the data type of each measurement variable. Include any additional methods for subgroup analysis or auxiliary analysis. If there are personnel reductions during the trial, indicate whether an intention-to-treat (ITT) analysis was used and compare it with per-protocol (PP) analysis]***

The primary and secondary indicators of this study's scales will be presented to participants in the form of paper questionnaires, while behavioral data and EEG data will be collected from participants using electroencephalography devices.

Demographic data and scale data analysis will use SPSS software, employing t-tests, covariance analysis, etc.; EEG data analysis will utilize Matlab_2013b software, EEGLab software, and scripts.

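### The aim of showing impaired executive function in IGD rests on an unnamed, non-randomised comparison with recreational gamers, while the only matching planned is between the training arms

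*Protocol*

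**What the plan says.** The Objective section puts a comparative question first: "this study aims to investigate whether the three sub-components of executive function in individuals with internet gaming addiction are impaired". The effect of the one-week training comes second. No reference group is named for the impairment question.

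The inclusion criteria admit two populations. Criterion 7 reads: "For recreational gamers: IAT score < 50, DSM-5 score < 5". Criterion 6, for IGD participants, sets the opposite cut-offs on both instruments and adds "gaming history exceeding 2 years, and gaming time of more than 14 hours per week". Criterion 7 has no condition on history or hours.

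The Sample size estimation section fixes the mix and the matching: "A ratio of 2:1 will be used to include 20 recreational gamers in the intervention group", and then "we will recruit an additional 61 participants with matching demographic profiles and equivalent levels of IGD (Internet Gaming Disorder) severity for the control group".

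The section on randomization allocates only the type of training, breath meditation or relaxation, and does so after baseline data are collected. On selection, the Participant recruitment section says: "Participants will be selected based on their order of participation according to inclusion and exclusion criteria". The Statistical analysis methods section says: "Demographic data and scale data analysis will use SPSS software, employing t-tests, covariance analysis, etc". It names no covariates and no contrast between IGD and recreational gamers.

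**The concern.** Impairment has meaning only against a reference group. Recreational gamers are the only candidates in the trial, and IGD status is a characteristic people bring with them. Randomising the training therefore gives no protection to the comparison of IGD participants with recreational gamers.

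The one matching step concerns a different contrast, mindfulness arm against relaxation arm, which random allocation already addresses. No step brings recreational gamers into line with IGD participants on age, gender or year of study. The two groups are also set apart on gaming exposure by the entry criteria themselves.

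At stake is the answer to a stated aim. A baseline difference on the Stroop, shifting or N-back task could be reported as impairment due to IGD when it partly reflects who volunteered or how much they play. A real impairment could equally be masked.

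**Working it through.** **The plan's own figures, and what they are for.** All inputs are from Sample size estimation: expected change 125 ms, SD 250 ms, two-sided α 0.05, power 0.80, paired t-test.

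- d = 125 / 250 = 0.5. The noncentral t calculation gives n = 33.37, rounded up to 34. The stated 34 is reproduced.
- 34 × 1.2 = 40.8, rounded up to 41 IGD participants. At 2:1, 41 / 2 = 20.5, taken as 20 recreational gamers. 41 + 20 = 61 per arm, and 2 × 61 = 122.

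These figures follow from a within-person change after training. None was derived for IGD against recreational gamers.

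**Can the matching sentence be read as covering that contrast?** No. It concerns the control group, which the randomization section defines as relaxation training. It also asks for equivalent IGD severity, which recreational gamers cannot have, because criterion 7 defines them by scores below the IGD cut-offs.

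**Illustration of size.** The documents give neither an imbalance nor a correlation, so both are assumed.

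- Group sizes: 2 × 41 = 82 IGD and 2 × 20 = 40 recreational. This assumes the control arm mirrors the intervention arm; the protocol states the 20 only for the intervention arm.
- Let one unmatched covariate differ by D SD between the groups and correlate r with reaction time within groups. With no true impairment, the spurious difference is r × D in SD units.
- SE in SD units = √(1/82 + 1/40) = 0.193. With the plan's 250 ms, SE = 48.2 ms.
- For D = 0.5 and r = 0.3, bias = 0.15 SD = 37.5 ms, and 37.5 / 48.2 = 0.78 SE. The false-positive rate P(|Z + 0.78| > 1.96) is about 12.2% by the normal approximation and 12.0% by noncentral t.

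The range at 82 against 40, by noncentral t with nominal 5%:

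| D | r | Bias (ms) | False-positive rate |
| --- | --- | --- | --- |
| 0.3 | 0.1 | 7.5 | 5.3% |
| 0.3 | 0.2 | 15 | 6.1% |
| 0.5 | 0.3 | 37.5 | 12.0% |
| 0.8 | 0.3 | 60 | 23.5% |
| 1.0 | 0.5 | 125 | 73% |

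The millisecond values borrow an SD from a paired calculation, where it acts as the SD of within-person change; the between-person SD of an averaged baseline may differ. The rejection rates do not depend on it, because the SD cancels in bias / SE.

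**The case against.** **The comparator is an inference.** The protocol names none, and the figure showing the overall design is not available. The Research background gives recreational gamers another possible role, to test mindfulness in healthy people, and the Study design section frames superiority around training in IGD. This stands as a caveat. But no other non-IGD group is recruited, so if the impairment aim is to be answered within the trial, this is the contrast that answers it.

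**The groups share much already.** A reader might infer that nothing makes them comparable. That goes too far. Both must be right-handed, aged 18 to 40, with PHQ-9 below 20 and GAD-7 below 11, with no history of mental illness and no other addictions. All come from one campus, so the real spread of age and education is probably narrower than the criteria allow. These limits restrict the range of differences; they do not balance the groups within it.

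**Covariates belong in an SAP.** This is accepted. The protocol mentions covariance analysis and already collects age, gender, grade, PHQ-9 and GAD-7, so the absence of a covariate list is not counted as a fault. Who is recruited and which groups are matched is fixed in the protocol, and later adjustment cannot fully repair poor overlap.

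**Mood is not simply a confounder.** It is tempting to add depression and anxiety to the list of confounders. The Research background describes emotional distress as something uncontrolled gaming leads to. On that account, adjusting for mood could remove part of the effect sought.

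**Conclusion.** The point holds as a design weakness in the impairment aim. The aim has no named comparator, the only available contrast is observational, and the plan's matching is directed at the training arms instead. Demographic differences can bias the result, and gaming exposure differs by design because only IGD participants must meet history and hours thresholds.

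The documents do not support three stronger readings. First, the result is not shown to be confounded: the 12% is an illustration resting on an assumed imbalance, an assumed correlation and the inferred 82:40 split, and the mildest case tabulated is barely above 5%. Second, it would be wrong to say that the two groups differ only in IAT and DSM-5 scores, given the extra exposure criteria for IGD. Third, this confounding does not affect the randomised comparison of mindfulness with relaxation.

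It should be corrected before recruitment. The Study design section says the trial has not begun, and matching cannot be introduced once participants are enrolled.

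**What to change.** 1. In Objective, name the recreational gamers at baseline as the comparator for the impairment question.
2. In Sample size estimation, do not simply delete the matching sentence: it is the only text implying that the control arm has the same 41:20 mix. State that both arms hold the same ratio of IGD to recreational participants, achieved through the random allocation, for example by stratifying on IGD status.
3. Move the demographic matching to where it is needed: frequency-match recreational gamers to IGD participants on age band, gender and grade at screening.
4. Analyse the baseline task measures by covariance analysis adjusted for age, gender and grade, here or in the SAP. Add PHQ-9 and GAD-7 only in a sensitivity model, because mood may be a consequence of IGD.
5. Word the conclusion as an association with IGD that may partly reflect gaming exposure. Matching on demographics does not remove that difference.

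The cost is protocol wording and slightly slower recruitment of recreational gamers, since some volunteers will fall in cells already filled. No new measurements are needed.
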